#### Secondary Outcomes

The statistical analysis plan for secondary outcomes will be published separately. In short, the safety of the intervention will be assessed by comparing the incidence of both severe and resistant hypoglycemic events and severe gastrointestinal complications using the Cox proportional hazard analysis. Feeding intolerance will be analyzed using a mixed effects logistic model. Moreover, mixed models will be used for the assessment of other longitudinal data such as analyses of the course of ketones and other metabolic markers. Kaplan-Meier plots will be used to document time-to-event effects, and the time-to-event effect size will be estimated using the Cox proportional hazard analysis. All time-to-event analyses will be performed on data censored at 30 days. As death is a competing risk for the duration of care outcomes, nonsurvivors will be censored beyond the longest duration of such care required for survivors.

### Sample Size Calculation

To provide a careful estimate of the number of patients required to answer whether the intervention is feasible, we based the sample size on a (1) a fasting response with ketogenesis and (2) sufficient nutritional intake.

We calculated the sample size to detect a fasting response with ketogenesis. In adults who are critically ill (n=70), 12 hours of fasting increased ketones compared with full feeding periods (ketones +0.47, SD 0.07 mmol/L; *P*<.001) [40]. In a study of healthy children, ketones increased from 0.08 mmol/L in the fed state to 0.34 mmol/L (90% CI 0.02-1.78 mmol/L) after 15 hours of fasting [41]. Using these data, we assumed baseline ketones of 0.10 mmol/L (fed state) and 0.20 mmol/L in the fasted state, with an SD of 0.16 mmol/L. To perform additional per-protocol analysis, we increased the sample size by 30%. Ultimately, the sample size of 140 should be able to detect, with at least 90% power (2-tailed power) and 95% certainty, the assumed increase in mean ketone levels of 0.10 mmol/L. Regarding nutritional intake, we considered a reduction in cumulative (caloric) intake, corrected for PICU length of stay, of >33% in the intervention group as clinically relevant based on the currently available literature [2]. The sample size (N=140, 70 per arm) is expected to be able to detect, with at least 80% power (1-tailed power) and 80% certainty, a reduction of 33% in cumulative caloric intake.

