### Outcome Measures

#### Primary End Points

The primary outcome of this study will be the feasibility of a daily feeding and fasting cycle (*intermittent feeding* strategy) compared with a continuous 24 hours per day feeding strategy in critically ill children. The primary outcome is defined as the difference in ketosis (3-β-hydroxybutyrate levels) between the groups under the condition of noninferiority regarding caloric intake. The amount of nutritional intake is defined as the daily caloric intake as a percentage of the estimated REE based on the body weight–based or body weight and length–based Schofield equation.

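### Feasibility requires both a ketone test and a caloric noninferiority test to succeed, but only each test's separate power is stated, and the power of the combined rule cannot exceed the weaker one

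*Protocol article*

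**What the plan says.** Under Primary End Points, the protocol article names feasibility as the primary outcome and defines it in one sentence: "The primary outcome is defined as the difference in ketosis (3-β-hydroxybutyrate levels) between the groups under the condition of noninferiority regarding caloric intake". The Hypothesis section has the same two-part form: more ketogenesis with no loss of daily intake.

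Under Primary Outcomes in the statistical section, the parts are tested separately: a two-tailed t test on ketones, and a linear mixed model for caloric intake with a 33% margin. General Rules sets the levels at two-sided P<.05, and one-sided P<.025 for noninferiority.

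The Sample Size Calculation section ties N to the feasibility question: "To provide a careful estimate of the number of patients required to answer whether the intervention is feasible, we based the sample size on" two components, ketogenesis in response to fasting and adequate nutrition. For ketones, "we assumed baseline ketones of 0.10 mmol/L (fed state) and 0.20 mmol/L in the fasted state, with an SD of 0.16 mmol/L", and N=140 is said to detect, "with at least 90% power (2-tailed power) and 95% certainty, the assumed increase in mean ketone levels of 0.10 mmol/L". For calories, "The sample size (N=140, 70 per arm) is expected to be able to detect, with at least 80% power (1-tailed power) and 80% certainty", a 33% reduction in cumulative intake. No power is given for meeting both conditions.

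**The concern.** A claim of feasibility needs both results. Ketosis with a failed caloric test does not satisfy the definition, and neither does the reverse. The probability that two tests both succeed is never above that of the less powerful one and is usually below it. The section asks how many patients are needed to answer the feasibility question, but the figures it gives answer two narrower questions.

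A reader who takes 90% or 80% as the chance that a truly feasible strategy will be declared feasible has the wrong quantity. This matters because Strengths and Limitations makes a larger trial conditional on this one showing safety and feasibility. A failure on either component could be over-read if the chance of missing the combined target is not known.

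**Working it through.** **Inputs from the article**
- Ketones: difference 0.20 − 0.10 = 0.10 mmol/L, SD 0.16, two-sided 0.05, 90% power, 30% inflation, N=140 (70 per arm).
- Calories: 33% margin; 80% power, one-tailed, at 80% certainty (Sample Size Calculation); one-sided 0.025 for the actual test (General Rules).
- Not given, so treated as assumptions: the caloric SD, the assumed true difference in intake, and the correlation between the two test statistics.

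**Step 1: reproduce N.** n per arm = 2(z₀.₉₇₅ + z₀.₉₀)²(SD/difference)² = 2 × (1.960 + 1.282)² × (0.16/0.10)² = 53.8, so 54. Then 2 × 54 = 108, and 108 × 1.3 = 140.4. This matches 140. The caloric 80% cannot be reproduced without an SD.

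**Step 2: ketone power at 70 per arm.** 0.10 / (0.16 × √(2/70)) = 3.70, and Φ(3.70 − 1.96) = 0.959. The t-based value is 0.957. The 90% belongs to the 54 per arm before inflation, whereas the primary analysis is by intention to treat.

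**Step 3: joint power.** For component powers p₁ and p₂, joint power lies between p₁ + p₂ − 1 and min(p₁, p₂), and equals p₁p₂ under independence.

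| Ketones | Calories | Worst case | Independent | Ceiling |
|---|---|---|---|---|
| 0.90 (printed minimum) | 0.80 | 0.700 | 0.720 | 0.80 |
| 0.957 (70 per arm) | 0.80 | 0.757 | 0.766 | 0.80 |

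With a bivariate normal model at correlations −0.5, −0.3, 0, +0.3 and +0.5, the first row gives 0.703, 0.708, 0.720, 0.737 and 0.751. At 70 per arm (normal-approximation ketone power 0.959) the values are 0.759, 0.761, 0.767, 0.776 and 0.784.

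**Step 4: the caloric error level.** If true intake is equal and the 80% is exact at one-sided level α, then margin/SE = z₁₋α + 0.8416, and power at one-sided 0.025 is Φ(margin/SE − 1.960).
- α = 0.20: margin/SE = 0.8416 + 0.8416 = 1.683; Φ(−0.277) = 0.391. Joint power with the ketone test at 70 per arm: 0.350 worst case, 0.375 independent, 0.391 ceiling.
- α = 0.10 (80% certainty read as a two-sided level): margin/SE = 1.2816 + 0.8416 = 2.123; Φ(0.163) = 0.565. Joint power: 0.524, 0.542 and 0.565.

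**Step 5: how it could be higher.** For illustration only, take the margin as 33 points of REE and the between-child SD as 40 to 60 points. With equal true intake at one-sided 0.025:
- SD 60: SE = 60√(2/70) = 10.14, and Φ(33/10.14 − 1.960) = 0.902.
- SD 40: SE = 6.76, and power is 0.998.

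With ketone power 0.957, independent joint power is 0.957 × 0.902 = 0.863 to 0.957 × 0.998 = 0.955. If intake were truly 15 points lower, caloric power would be 0.427 (SD 60) to 0.759 (SD 40), and independent joint power 0.409 to 0.726.

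**The case against.** The best defence is that nothing printed is miscalculated. N=140 reproduces, each power is labelled with its own component, and no joint power is claimed. A condensed article may leave detail to the full protocol. Under the article's own hypothesis of unchanged intake, and with the SDs assumed in Step 5, joint power is about 86–96%. Both powers are stated as minimums. Enrolment stood at 132 of 140, and neither design nor tests would change.

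Most of this stands. It shows that this is a fault in what the power statement describes, not an arithmetic error, and that low power has not been demonstrated. It does not remove the point: the article printed the calculation and said it was sized to answer whether the strategy is feasible, and the figures given are not the power of that rule.

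Two stronger readings are tempting. A reader might infer that the trial has only 70–72% power. Those values combine the two printed minimums (0.90 + 0.80 − 1, and 0.90 × 0.80). They ignore the article's own ketone inputs, which give 95.7% at 70 per arm, so they are not the power at N=140. A reader might also infer that the two tests are negatively correlated, since the Introduction links low macronutrient intake to ketogenesis. That is plausible, but no correlation is reported, and Aims says no data exist on when the fasting response begins in these children. Taking the printed minimums, negative correlation lowers joint power by at most 2 points (0.720 to 0.700).

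**Conclusion.** The point holds as a correction to the power statement. The primary outcome is a conjunction and its power is not given. With caloric power taken as exactly 80%, joint power at 70 per arm is about 76–77% at zero or negative correlation, and never above 80%.

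The actual value is not fixed by the document, in either direction. It could be higher, because both powers are minimums and the caloric SD is missing. It could be about 35–56% if the 80% is exact at one-sided 0.20 or 0.10 and true intake is equal, because the analysis uses one-sided 0.025. The caloric 80% is also worded as power to detect a reduction, which is not the probability of concluding noninferiority, so carrying it into a joint figure is itself an assumption.

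A reader should therefore not conclude that the trial is too small or that more patients are needed. The document supports neither.

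**What to change.** In Sample Size Calculation:
- state that feasibility requires both tests to succeed;
- give the caloric SD and the assumed true difference in intake, and say whether the 33% is in points of REE or relative to control intake;
- replace the two separate claims with the joint power at N=140, computed at the levels in General Rules (two-sided 0.05 for ketones, one-sided 0.025 for caloric noninferiority) and shown over a range of correlations.

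Do not print a guarantee of at least 70% unless that calculation supports it, because the 80% was stated at a different error level. The cost is a sentence or two and a short calculation. The stated power may become less favourable. No patients, tests or decision rules change.

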### Statistical Analysis

#### General Rules

A CONSORT (Consolidated Standards of Reporting Trials) flow diagram will be reported [39]. All analyses will be primarily performed according to an intention-to-treat analysis. To perform additional per-protocol analysis, we anticipated that up to 30% of the patients will not be able to receive artificial nutrition during their admission to the PICU.

Categorical variables will be summarized as counts and frequencies and analyzed using the chi-square test or Fisher exact test. Continuous variables will be summarized using either mean and SD or median and IQR, depending on the distribution of the variables.

All analyses will be performed primarily for the complete group. In secondary analyses, analyses can be stratified according to different age groups (neonates, infants, and children). Adjustment for baseline risk factors, including the diagnostic group, age group, severity of illness, and severity of nutritional risk, will only be used for secondary analyses. Multiple imputation will only be used in secondary analyses to deal with missing data for confounders. For all end points, differences will be considered statistically significant when the 2-sided *P* value is <.05 or when the 1-sided *P* value is <.025 in the case of noninferiority tests, without correcting for multiple testing.

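### The 30% allowance multiplies by 1.3 instead of dividing by 0.7, leaving about 86–87% per-protocol ketone power at the 30% maximum; whether 0.10 mmol/L is the intention-to-treat difference is not stated

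*Protocol article*

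**What the plan says.** All places are in the protocol article.

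- **Sample Size Calculation**, effect size: "we assumed baseline ketones of 0.10 mmol/L (fed state) and 0.20 mmol/L in the fasted state, with an SD of 0.16 mmol/L".
- Same section, allowance: "To perform additional per-protocol analysis, we increased the sample size by 30" percent.
- Same section, claim: "the sample size of 140 should be able to detect, with at least 90% power (2-tailed power) and 95% certainty", for the assumed mean increase of 0.10 mmol/L. The total is 140, 70 per arm.
- **Statistical Analysis, General Rules**, reason for the allowance: "we anticipated that up to 30% of the patients will not be able to receive artificial nutrition during their admission to the PICU".
- Same section, analysis set: "All analyses will be primarily performed according to an intention-to-treat analysis". The significance level is two-sided 5%.
- **Statistical Analysis, Primary Outcomes**: the ketone comparison is a two-tailed t test. Each child's value is the mean of the peak ketone levels over the fasting periods, with matching times in the control arm.

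**The concern.** There are two separate issues.

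The first is arithmetic. An allowance for losing a fraction f of the sample must divide the required number by 1 − f. Multiplying by 1 + f always falls short: at f = 0.30, 1.3 × 0.7 = 0.91, so only 91% of the required number survives the loss the allowance was set for.

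The second concerns what 0.10 mmol/L means. It is presented as a contrast between fed and fasted states, supported by studies that compared the two. A child who cannot receive artificial nutrition is not fed by the study route in either arm, so allocation may create little or no ketone contrast in that child. The per-protocol set removes such children, but the primary intention-to-treat set keeps them. The sample-size text does not say whether 0.10 already allows for them.

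Ketosis is one half of the primary outcome. If the ketone test is not significant, readers will use the stated power to judge whether a fasting response has been ruled out, so the figure should say which analysis set and which difference it belongs to.

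**Working it through.** **Inputs.** From Sample Size Calculation: difference Δ = 0.20 − 0.10 = 0.10 mmol/L; SD 0.16; power 90%; 70 per arm; 30% increase. From General Rules: two-sided α = 0.05; up to 30% of children unable to receive artificial nutrition; intention-to-treat primary.

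**Step 1: reproduce the plan's number.**

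n per arm = 2 × (1.960 + 1.2816)² × (0.16/0.10)² = 53.8, so 54 per arm or 108 in total. The exact noncentral t calculation gives 55 per arm or 110 in total.

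- Multiplying: 108 × 1.3 = 140.4, which is the plan's 140.
- Dividing: 108/0.7 = 154.3, so 155 (156 with equal arms). From the exact t base, 110/0.7 = 157.1, so 158.

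One-sided and two-sided tests at 80%, 90% and 95% power were tried with both factors. Only the two-sided 90% case multiplied by 1.3 gives 140.

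**Step 2: per-protocol power at the anticipated maximum loss.**

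140 × 0.7 = 98, or 49 per arm. The noncentrality is 0.10/(0.16 × √(2/49)) = 3.09. Power is Φ(3.09 − 1.96) = 87.2% by the normal approximation and 86.5% by exact t.

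The largest loss that keeps 90% is 1 − 55/70 = 21.4% (exact t) or 1 − 54/70 = 22.9% (normal).

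**Step 3: intention-to-treat power at 70 per arm.**

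If 0.10 mmol/L is the difference across all randomised children, the noncentrality is 0.10/(0.16 × √(2/70)) = 3.70. Power is 95.9% (normal) or 95.7% (exact t).

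Now assume instead that 0.10 holds only in fed children, that a share f is unfed and contributes no difference, and that all children are measured. The expected difference is 0.10 × (1 − f):

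| Share unfed | Difference (mmol/L) | Power, normal | Power, exact t |
|---|---|---|---|
| 0% | 0.100 | 95.9% | 95.7% |
| 10% | 0.090 | 91.4% | 91.1% |
| 20% | 0.080 | 84.1% | 83.6% |
| 30% | 0.070 | 73.5% | 72.9% |

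Under these assumptions power crosses 90% at about 12% unfed. At 30%, adding the extra variance from mixing fed and unfed children in the intervention arm (0.3 × 0.7 × 0.10²) lowers 72.9% to 71.2%.

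If unfed children had no usable ketone value and dropped out of the t test, the 30% case would return to 49 per arm and 86.5%.

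**The case against.** **The power claim is attached to 140 children, not to the per-protocol set.** This is literally so, and the per-protocol analysis is described as additional. Increasing the sample by 30% is also exactly what was done. But the only reason given for the increase is the per-protocol analysis, and the base of 108 is the number that gives 90%. An allowance built that way is naturally read as protecting 90% in that set, and at the 30% maximum it does not. What stands is that the gap is small, about 3 to 4 points, and appears only when losses exceed about 21%.

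**The primary analysis is adequately powered as stated.** This also stands, on the protocol's own terms: at 0.10 mmol/L and 70 per arm the power is about 96%. A reader might infer that the intention-to-treat analysis simply lacks 90% power, or that its true power is 73%. The document does not support that. The 73% needs four things at once: the full 30%, which the protocol gives as an upper limit; exactly no contrast in unfed children; a ketone value for all of them; and a 0.10 that does not already allow for them. The protocol states none of these.

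**0.10 may already be discounted.** The cited increases are 0.47 mmol/L in critically ill adults and 0.34 − 0.08 = 0.26 mmol/L in healthy children. A difference of 0.10/0.7 = 0.143 mmol/L in fed children, diluted by 30%, would still be 0.10 overall, and 0.143 is below both cited increases. So a trial-wide 0.10 cannot be excluded. Equally, the text labels the two means as fed and fasted states and mentions no discount, so the question is open.

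**Conclusion.** The arithmetic slip is established from the document. The allowance was applied as 108 × 1.3 = 140 rather than 108/0.7, a difference of about 15 to 18 children. At the anticipated maximum of 30% the per-protocol set has about 86–87% power for 0.10 mmol/L, not at least 90%. This rests only on the stated difference, SD and significance level, and on equal loss in both arms.

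The intention-to-treat point is conditional. Power is about 96% if 0.10 is the difference across all randomised children. It is about 91%, 84% or 73% at 10%, 20% or 30% unfed if 0.10 belongs to fed children only and unfed children are measured and add nothing. What the protocol fixes badly is that it leaves the meaning of 0.10 undefined while expecting up to 30% of its primary population not to be artificially fed. The stated power is not shown to be wrong for the primary analysis.

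**What to change.** Keep N=140; 132 children were already included by 12 May 2022 according to the Results section. In Sample Size Calculation:

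1. State that the 30% increase leaves 98 children (49 per arm) at the maximum anticipated loss, with about 86% per-protocol power for 0.10 mmol/L, and that 90% is kept up to about 21% loss.
2. Say whether 0.10 mmol/L is the difference expected across all randomised children or only among those artificially fed.
3. If it is the former, the existing power statement can stay for intention-to-treat; add that unfed children are already allowed for. If it is the latter, replace the unqualified claim with a conditional range: about 91%, 84% and 73% at 10%, 20% and 30% unfed, assuming that those children contribute no difference.

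The cost is a few sentences. The sample size, the analysis and the conduct of the trial do not change. The stated per-protocol power becomes slightly less favourable, as does the intention-to-treat power if the second reading applies.

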#### Primary Outcomes

To assess a significant difference in ketosis between the 2 arms, a 2-tailed *t* test will be performed on the patient means of the highest ketone levels in each fasting period (or similar time point in the control group). A linear mixed model will be used to assess the noninferiority of caloric intake (repeatedly measured over time) in the intervention group, with a noninferiority margin of 33%.

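### The stated 80% power for the caloric-intake condition belongs to a looser test than the planned one-sided 0.025 noninferiority test, so the power of the planned test is not known

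*Protocol article*

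**What the plan says.** The Primary End Points section defines the primary outcome as the "difference in ketosis (3-β-hydroxybutyrate levels) between the groups under the condition of noninferiority regarding caloric intake". Caloric noninferiority is thus a condition on the primary result.

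Three places in the protocol article then bear on that condition:

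- **Sample Size Calculation** gives its power. The 140 patients, half in each arm, are said to suffice to reveal, "with at least 80% power (1-tailed power) and 80% certainty, a reduction of 33% in cumulative caloric intake". The quantity named is corrected for length of PICU stay.
- **General Rules** sets the test level. A result counts as significant "when the 1-sided *P* value is <.025 in the case of noninferiority tests, without correcting for multiple testing".
- **Primary Outcomes** (Statistical Analysis) names the test, a linear mixed model. Its target is "noninferiority of caloric intake (repeatedly measured over time) in the intervention group, with a noninferiority margin of 33" (per cent).

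For ketones, the Sample Size Calculation pairs a two-tailed calculation with 95% certainty and at least 90% power. That agrees with the two-sided 5% level in General Rules.

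**The concern.** The power of a test is tied to its error level. Here the level behind the power figure and the level of the planned test differ, for the same endpoint and the same 33%, and nothing in the document reconciles them. The ketone sentence suggests that certainty means one minus the error rate. On that reading, 80% certainty in a one-tailed calculation is an error of 0.20, eight times the planned 0.025. Even on the more lenient reading, a two-sided 80% interval, the one-sided error is 0.10, four times the planned level.

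The wording points at a different question too. Power to detect a 33% reduction is the chance of finding a shortfall that exists. The planned test needs the chance of ruling out such a shortfall when there is none.

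The stake is how the primary result is read. Someone who takes 80% as the power of the planned test would give a failure to show noninferiority more weight than the document can support.

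**Working it through.** **Inputs from the document.** 70 per arm; at least 80% power, one-tailed, at 80% certainty; 33% margin; noninferiority test at one-sided 0.025. Ketones: difference 0.10 mmol/L, SD 0.16 mmol/L, two-sided 5%, 90% power, 30% increase.

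**Step 1. Where N=140 comes from.** Ketone inputs: n per arm = 2 × (1.960 + 1.282)² × 0.16² / 0.10² = 53.8, so 54 per arm and 108 in total. 108 × 1.30 = 140.4. This reproduces 140. The total therefore follows from the ketone calculation, and the caloric figure reads as a statement about a size already reached.

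**Step 2. The caloric 80%.** It cannot be rebuilt, because the article gives no SD for caloric intake. That is detail an article may leave to the full protocol, and the comparison of levels does not need it.

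**Step 3. What the statement implies.** For a normal test, power = Φ(margin/SE − z(1−α)). The same expression serves for detecting a true 33% reduction and for excluding one when the true difference is zero, so the wording does not alter the conversion. Setting power at exactly 80%:

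| Reading of 80% certainty | Implied margin/SE | Power at one-sided 0.025 |
|---|---|---|
| one-sided 0.20 | 0.842 + 0.842 = 1.683 | Φ(1.683 − 1.960) = 39% |
| one-sided 0.10 | 1.282 + 0.842 = 2.123 | Φ(2.123 − 1.960) = 56% |

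**Step 4. Are these the actual power?** No: the text says at least 80%. Take the margin as 33 points of REE, a true difference of zero, 70 per arm and a simple comparison of patient means, so SE = SD × √(2/70). The SDs below are assumptions.

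| Assumed patient-level SD (points of REE) | SE | margin/SE | Power at one-sided 0.025 |
|---|---|---|---|
| 50 | 8.45 | 3.905 | 97% |
| 60 | 10.14 | 3.254 | 90% |
| 70 | 11.83 | 2.789 | 80% |
| 80 | 13.52 | 2.440 | 68% |
| 100 | 16.90 | 1.952 | 50% |
| 116 | 19.61 | 1.683 | 39% |

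The planned test has 80% power if the SD is about 70 points or less. The 39% floor needs an SD of about 116 points.

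**The case against.** The strongest reply is that the floors are remote. The plan says at least 80%, and the sample size was set by ketones, so caloric power was never solved to be exactly 80%. An SD of 116 points is hard to reach: patient means lying between 0 and 200% of REE cannot have an SD above 100 points, and means between 0 and 100% cannot exceed 50. The Caloric Intake section targets 1×REE at the end of the first week, with later maxima of 1.3×REE in older children and up to 2×REE in neonates and infants. This largely stands. It has two limits: targets are not caps on delivered intake, and if the 33% is relative to the control mean, the 39% floor corresponds to a coefficient of variation of 0.33 × 3.515 = 1.16, which these bounds do not exclude.

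A second reply is that the planned test is stricter than the level used for sizing, so the mismatch cannot increase false claims of noninferiority. That is correct.

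A third is that 132 of 140 patients had been enrolled by May 2022, so a recalculation cannot change the design. Also correct, but it does not make the printed figure right.

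A reader might go further and infer that the trial has 39% power for this condition, or about 35% for both parts of the primary outcome (0.90 × 0.39). The documents do not support either. The first treats a floor as an estimate. The second multiplies two floors and assumes independence, whereas the stated ketone inputs with 70 per arm give Φ(0.10/(0.16 × √(2/70)) − 1.960) = Φ(3.698 − 1.960) = 96%, not 90%.

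**Conclusion.** The inconsistency holds. The caloric power statement uses a looser error level than the planned test and describes detection instead of exclusion, so its 80% is not the power of the noninferiority test on which the primary outcome depends.

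The statement by itself secures only about 39% or 56% at one-sided 0.025, depending on how 80% certainty is read. Both figures assume a true difference of zero and a normal approximation. Actual power is unknown from this document and may be 80% or more: about 90% to 50% for assumed SDs of 60 to 100 points of REE.

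The point concerns an incorrect power statement about a primary condition. It does not show that the trial is too small, that the test level is wrong, or that the margin is wrong. It should be fixed, but it does not threaten the validity of the analysis.

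**What to change.** Keep N=140 and the one-sided 0.025 test. In the Sample Size Calculation:

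1. Delete the 80% certainty.
2. Recompute the power at one-sided 0.025 for excluding a 33% reduction when the true difference is zero, and state the SD used.
3. Reword the sentence so that it speaks of excluding the reduction.

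Power at the per-protocol size (140 × 0.70 = 98) and joint power with ketones could be added, but are optional. The restatement is best made before results are known, so that neither the power figure nor the test level looks chosen after the fact.

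The cost is one recalculation and a wording change, with no extra patients. The downside is that the stated power may turn out less favourable than 80%.
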